### Study design overview

A prospective effectiveness-implementation hybrid design [70] involving pre-post intervention evaluation with matched controls will be used to implement and evaluate the HKTP. Due to design, matched control sites were pre-specified, and were matched with intervention sites based on city population size, Hispanic proportion of the city population, and kidney transplant and LDKT volumes. Although an ideal study design would be a randomized controlled trial that randomizes patients within each center, it is laden by contamination effects. Randomizing at the center level would require a large number of centers to serve as intervention sites and controls, which is costly. To assess other secular trends, data from matched control centers that do not implement the HKTP will be compared. Control sites were selected in different cities than intervention sites to avoid contamination from local implementation efforts. The first year will focus on implementing the HKTP at BUMC and MC over a 12-month period (Aim 1). Remaining years will focus on evaluating the HKTP on Hispanic LDKTs and on program fidelity in years 2–4½ (Aims 2 and 3).

The hypotheses are that the HKTP will lead to a(n):H_1_ Increase in the ratio of Hispanic to non-Hispanic white LDKTs and in the number of Hispanic LDKTsH_2_ Increase in the number of Hispanic ESRD patients added to the waiting listH_3_ Increase in the number of Hispanic potential donors per potential recipientH_4_ Greater satisfaction of Hispanic ESRD patients with culturally competent care

AIM 1: To implement the HKTP at Two Transplant Centers.

The NU team will first provide BUMC and MC with a preliminary set of protocols comprising the HKTP manual of operations, scripts for clinical coordinator and outreach staff to use, and educational materials describing the structure and content of the education sessions and transcriptions. To train the staff and providers at BUMC and MC, a video-based curriculum will be provided that explains the outreach staff’s communications with dialysis patients, and demonstrates NM’s HKTP Director’s education sessions. NM’s HKTP education session PowerPoint slides will also be provided for sites to use. The set of protocols will help BUMC and MC to determine how to modify their organizations to accommodate the HKTP. Publications that provide evidence to support the HKTP’s increase in Hispanic LDKTs will be provided to foster site ‘buy in’ to implement the HKTP [20, 68].

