### Outcome measures

We will assess the reduction in disparities between self-identified Hispanics and non-Hispanic whites in LDKT rates for adult-to-adult living kidney donation. The effectiveness of the HKTP will be assessed by comparing the outcomes before introducing the HKTP and after the HKTP has been fully implemented. Measures will be collected at intervention and control sites in pre and post periods. For the final outcome measures, de-identified, aggregate center-level data will be collected from the Organ Procurement and Transplant Network/United Network for Organ Sharing (OPTN/UNOS) as publically reported data (Table 2). Data from sites’ medical record review will also be collected. Intermediate outcome measures about each Hispanic and non-Hispanic white potential recipient and potential donor will be collected monthly by research directly from intervention and control sites by medical record review to assess the pathways by which the HKTP potentially increases rates of Hispanic LDKT. We expect that the pre-post change will demonstrate a higher number of potential donors who initiate evaluation and complete more steps in the donor evaluation process.

**Table 2 Tab2:** Final and Intermediate outcome measures: transplant center-reported

Construct	Measure description
Final outcomes	
Ratio of Hispanics to Non-Hispanic Whites Receiving LDKTs	This ratio takes into account growth in transplant center volume while also providing a comparison to non-Hispanic whites, necessary for assessing disparities in LDKT [102]. The ratio provides an index of whether the Hispanic LDKT increase has grown over and above the increase observed at a center overall. By using this ratio, factors related to the center’s infrastructure and capacity to perform additional LDKTs that affect both Hispanics and non-Hispanic whites equally are accounted for. Institutional commitments to LDKT that are associated with higher rates of LDKT, can influence willingness to donate or preferences for LDKT, and affect both populations equally (e.g., paired donation, and desensitization efforts), are accounted for.
Number of Hispanic LDKTs	Change in number of Hispanic LDKTs compared to change in number of non-Hispanic white LDKTs will provide evidence that the increase is not at the expense of white patients.

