### Statistical analysis plan

SAS version 9.4 (Carey, NC) will be used for analyses. Testing of each hypothesis will be performed separately for each study site. For Hypotheses 1 and 2, quarterly UNOS outcome data (6 years pre- and 3.5 years post-HKTP) will be used to model ethnic and racial differences in transplants, to account for external events that could alter LDKT rates, and to analyze the sustainability of the HKTP intervention. Hypotheses 3 and 4 will be evaluated with monthly data. Associations between final outcome and intermediate outcome measures, and individual patient and donor level variables will be evaluated. Matched intervention and control sites will be compared.

To test hypothesis 1, we will use OPTN/UNOS data, to construct the ratio of the number of Hispanics receiving LDKTs to the number of non-Hispanic whites receiving LDKTs for each center from 6 years prior to 3.5 years after implementation of the HKTP. An interrupted time series (ITS) design with segmented regression analysis will be used to assess the HKTP. Ratio data will be collected across 24 quarterly time points pre-intervention (reference point), and 14 time periods post-intervention for a total of 38 time-series data points for each center.

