We recognize some study limitations and identified ways to overcome those threats. First, the 3.5 year study period may yield conservative estimates; however, at NM®, most transplant candidates who receive a LDKT, do so between 6 and 18 months after completing evaluation. Second, there may be “spill over” of HKTP benefits to non-Hispanic whites. While favorable to society, spill over would support the null hypothesis. However, using number of Hispanic LDKTs as an outcome measure will control for this prospect. Third, it may be challenging to identify which HKTP components are most effective in contributing to the outcomes. However, we will map intervention components to intermediate outcomes, and map intermediate outcomes to final outcomes. Fourth, if we find a lack of significant increase in LDKT rates, then fidelity evaluation, and patient- (demographic) and national-level factors (i.e., media publicity about LDKT) will be assessed for broader LDKT trends.

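### The interrupted time series has one break, no stated place for the 12 implementation months and no allowance for the protocol's own 6 to 18 month delay to LDKT

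*Protocol article*

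**What the plan says.** The Statistical analysis plan section says: "An interrupted time series (ITS) design with segmented regression analysis will be used to assess the HKTP". For H1 the ratio is built "from 6 years prior to 3.5 years after implementation of the HKTP", giving 24 quarterly points before the intervention and "14 time periods post-intervention for a total of 38 time-series data points for each center". H2 uses quarterly data over the same window. No transition segment, phase-in or lag term is described.

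Other sections bear on where the break falls:
- Study design overview: "The first year will focus on implementing the HKTP at BUMC and MC over a 12-month period". Evaluation occupies years 2 to 4½.
- Study design overview, Aim 1 text: monitoring is scheduled for implementation in months 0 to 8, adjustment in months 9 to 12 and process checks in months 13 to 54.
- Outcome measures: effectiveness is judged by "comparing the outcomes before introducing the HKTP and after the HKTP has been fully implemented". The same section labels the year 1 satisfaction surveys as pre-HKTP.
- Discussion, limitations: the 3.5-year period may give conservative estimates, but at the coordinating center "most transplant candidates who receive a LDKT, do so between 6 and 18 months after completing evaluation".

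**The concern.** Two things are left loose in a design whose point count is otherwise fixed.

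First, the implementation year has no stated place. Months 13 to 54 use up all 14 post quarters. The wording in Outcome measures suggests that year 1 belongs to neither period, while the survey label treats it as pre. The phrase that anchors the series does not say whether implementation means its start or its completion. If year 1 sits in the pre segment and patients are already being reached, the pre-trend tilts upward and the projected counterfactual is too high.

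Second, the protocol's own interval implies that a transplant effect builds up over roughly post quarters 3 to 6 for patients who complete evaluation at the break. A test of an immediate step or level change would understate that effect. A break date or lag chosen after the data are seen could decide H1.

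**Working it through.** **The plan's own figures.** 6 years × 4 = 24; 3.5 years × 4 = 14; 24 + 14 = 38, as stated. Months 13 to 54 are 42 months, and 42 / 3 = 14 quarters, so the post segment matches the time after the implementation year.

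**Model and assumptions.** Noise-free least squares on y = b0 + b1·t + b2·P, with or without b3·P·(t − 25); t = 1 to 38 and P = 1 from quarter 25. The full effect is 1. Assumed LDKT shape: 0 until 6 months after exposure starts, linear to full at 18 months. The article gives neither the ramp nor the exposure date, so the date is varied.

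**LDKT, exposure from month 12.** Post-quarter values are 0, 0, 0.125, 0.375, 0.625, 0.875, then eight 1s. The sum is 10 and the mean 10/14 = 0.714.

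*Step only* (b2 = residualised cross-product / residualised sum of squares of P):
- Sum of squares: 24·14/38 − 168²/4569.5 = 8.842 − 6.177 = 2.665.
- Cross-product: 10·24/38 − (168/4569.5)·139.25 = 6.316 − 5.120 = 1.196.
- Estimate: 1.196/2.665 = **0.45**. SE: 1/√2.665 = 0.613 residual SD.

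*Level plus slope* (a separate line through the 14 post points, since the pre segment is flat):
- Slope change: 19.25/227.5 = 0.085 per quarter.
- At the break: 0.714 − 6.5·0.0846 = **0.16**. If the ramp instead runs in even steps (0.2, 0.4, 0.6, 0.8) to full at quarter 7, this is 0.17.
- At the last quarter: 0.714 + 6.5·0.0846 = **1.26**.
- Mean over post quarters 7 to 14: 0.714 + 3·0.0846 = 0.97 (0.96 with the even-step ramp).

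**Other exposure dates.** Same formulas. In the last column, t runs 1 to 24 and then 29 to 42.

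| Exposure starts | Mean share of effect, 14 post quarters | Step only, year 1 counted as pre | Step only, year 1 excluded |
|---|---|---|---|
| Month 12 | 0.71 | 0.45 | 0.39 |
| Month 8 | 0.81 | 0.61 | 0.57 |
| Month 0 | 0.96 | 0.82 | 0.91 |

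**Short-lag outcome, year 1 counted as pre.** Assume full effect from quarter 25 and part of it in quarters 21 to 24. The pre slope is Σ(t − 12.5)c / 1150, where c is the share of the effect in each quarter, and the line is projected forward.
- Mild uptake (0, 0, 0.25, 0.50): slope 8.375/1150 = 0.00728, mean 0.75/24 = 0.031. Projected excess at quarters 25, 31 and 38 is 0.12, 0.17 and 0.22, so the fitted effect is **0.88, 0.83 and 0.78** of truth.
- Strong uptake (0.25, 0.50, 0.75, 1.00): slope 26.25/1150 = 0.0228, mean 2.5/24 = 0.104. Projected excess is 0.39, 0.53 and 0.69, so the fitted effect is **0.61, 0.47 and 0.31**.

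**The case against.** The strongest reply is that segmented regression normally carries a slope term, and nothing in the article names the immediate level coefficient as the test. With the slope included, the unlagged model returns the post-period mean exactly (0.714) and about 0.96 of the full effect over post quarters 7 to 14. This stands. A reader might infer that the planned analysis is generally biased toward no effect. The documents do not support that, because the understatement applies to a step or level-change test. The low level value at the break is also not bias in itself, since the assumed true effect there is zero. The slope model does still misstate the shape: it rises past the plateau to 1.26, which matters because the section also wants to analyze sustainability.

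A reader might also infer that the implementation year has been put into the post segment. The 14 quarters match months 13 to 54, so it has not. Leaving year 1 out is a natural reading of Outcome measures, and the pre-HKTP label on year 1 concerns the surveys, not the registry series. So contamination is a risk under one of two readings and is not established.

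The Discussion already concedes conservative estimates, and a fuller analysis plan may specify the lag and the tested parameter. That limits the lag point to what should be fixed in advance. It does not settle the place of year 1, on which the article's own sections point in different directions.

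**Conclusion.** The point holds as a design ambiguity with a cheap remedy. It is not proof that the analysis will miss a working programme.

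- **Implementation year.** The sections must be reconciled. If year 1 is pre and exposed, short-lag effects shrink to about 0.8 to 0.9 of truth (mild uptake) or 0.3 to 0.6 (strong uptake). If it is excluded, this problem disappears. Applying this to H2 assumes that H2 uses the same segmented model; the article ties the model explicitly only to H1.
- **Lag.** A step-only test of LDKT outcomes recovers about 0.45 of the full effect with exposure from month 12, about 0.6 from month 8, and 0.8 to 0.9 from month 0. A level-plus-slope model preserves the average but gives about 0.16 to 0.17 at the break and 1.26 at the end in the month 12 case.

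The sizes rest on the assumed linear ramp, uptake shares and exposure dates, and on carrying the coordinating center's 6 to 18 month interval over to the study sites. That interval runs from completed evaluation: patients evaluated during year 1 shorten the effective lag, and time spent reaching completion lengthens it.

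**What to change.** State the break in calendar terms and use three segments: 24 pre quarters ending before HKTP introduction; the 4 implementation quarters as a transition excluded from both fitted segments, with calendar time kept; and 14 post quarters from month 13. Align the wording in Outcome measures and the Statistical analysis plan section.

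For LDKT outcomes, name the primary contrast in advance: either a lag or ramp term built on the 6 to 18 month figure, or the model-based effect averaged over post quarters 7 to 14. Use no LDKT lag for waitlist additions. Report the unlagged model as sensitivity. Set all this before outcome data are examined.

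The cost is wording and some precision, shown here in residual SD units with independent errors, SE = √(c′(X′X)⁻¹c). On the contiguous 38 quarters, a ramp term moves the SE from 0.61 to 0.64. Dropping the first 2, 4 or 6 post quarters from a step model gives 0.66, 0.71 or 0.76. With the four-quarter gap kept in calendar time, the ramp SE is about 0.67. The quarters 7 to 14 contrast from a level-plus-slope model is about 0.86 with the gap, against 0.76 without it, so the ramp term is the more precise option if its shape is accepted.

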## Methods and design

### Setting

The HKTP will be prospectively evaluated at two intervention sites: Baylor University Medical Center (BUMC) in Dallas, TX, and the Mayo Clinic in Phoenix, AZ. Both sites are located in cities serving the largest U.S. Hispanic (Dallas: 38.3%; Phoenix: 40.8%) and ethnic subgroup (Mexican) populations [66]. Intervention sites are matched with control sites by city population size, Hispanic proportion of the city population, and KT and LDKT volumes, including: Houston Methodist in Houston, TX (matched to BUMC), and University of Colorado Denver in Denver, CO (matched to MC). Control sites were selected in different cities than intervention sites to avoid contamination from local implementation efforts. As Northwestern Memorial Hospital (NMH)/Northwestern Medicine® (NM®) created the HKTP, but did not prospectively evaluate it, NMH/NM serves as the Study Coordinating Center. NMH/NM® is a nationally-recognized, academic teaching hospital, and includes one of the nation’s leading transplant centers.

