A probabilistic sensitivity analysis will be conducted to ascertain the likelihood that changes in the volume of LDKTs at study sites are indeed attributable to implementation of the HKTP. Rather than assigning a single value to each parameter, we will assign a distribution to all parameters in the model. The ranges will be determined by the average value, the standard deviation, and the shape of the spread of the data. A 1-way sensitivity analysis by varying one parameter at one time will be used to identify secular trend threshold values. We will collect intermediate outcome data at control sites to enable more nuanced pretest-posttest analyses. Sensitivity analyses using published [96, 97] and publically reported LDKT volume data from matched controls will be used to adjust for regional variability. In addition, the two transplant centers implementing the HKTP will be compared to each other. To assess the influence of innovative adaptations on outcomes, qualitative data from routine assessments of the modifications to the HKTP (Aim 2), collected at 14 quarterly time periods post-intervention, will be transformed into quantitative parameters, and will be incorporated into a longitudinal data analysis evaluating trend in outcomes over the post-intervention period accounting for quarterly time-varying adaptations.

We expect an increase in satisfaction scores before and after the education sessions by 10% in post-HKTP based on prior studies [98]. Differences in CAHPS composite scores will then be compared between pre- and post-HKTP by each site using a two-sample t-test. A total of 100 patients per site (50 pre-HKTP, 50 post-HKTP) provides 80% power to detect a difference of 10% (SD = 18%) in mean satisfaction scores before and after education sessions between pre- and post-HKTP groups using a two-sided t-test with a *p* = 0.05 significance level.

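### The probabilistic sensitivity analysis is given the job of saying how likely it is that LDKT changes are due to the HKTP; as described it conveys only parameter uncertainty within the assumed model, and one control per site cannot supply the missing piece

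*Protocol article*

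**What the plan says.** All references are to the protocol article.

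- **Purpose (Statistical analysis plan):** "A probabilistic sensitivity analysis will be conducted to ascertain the likelihood that changes in the volume of LDKTs at study sites are indeed attributable" to the HKTP.
- **Mechanism (same section):** "Rather than assigning a single value to each parameter, we will assign a distribution to all parameters in the model". The distributions come from the data: "The ranges will be determined by the average value, the standard deviation, and the shape of the spread of the data".
- **Companion analysis (same section):** "A 1-way sensitivity analysis by varying one parameter at one time will be used to identify secular trend threshold values".
- **Controls (Setting):** one per intervention site, namely "Houston Methodist in Houston, TX (matched to BUMC), and University of Colorado Denver in Denver, CO (matched to MC"). Sites were not randomised; Study design overview says "Due to design, matched control sites were pre-specified" and gives the controls the task of showing secular trends.
- **Unit of testing (Statistical analysis plan):** "Testing of each hypothesis will be performed separately for each study site". Each controlled comparison is therefore one centre against one centre.
- **Data:** H1 and H2 use quarterly OPTN/UNOS series, and H1 is analysed by segmented regression. Outcome measures describes the final-outcome data as aggregate, centre-level and publicly reported.

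**The concern.** Whether a rise in Hispanic LDKTs after the interruption is due to the HKTP depends on whether something else changed at that centre at about the same time. Drawing the parameters of a segmented model from distributions does not address this. The model has one term for the break, and any other cause acting at that date is absorbed into it. The draws then describe how precisely the break is estimated, not what caused it.

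A control centre helps with shifts that both centres share. To judge whether the remaining difference is unusual, one must know how far two untreated centres ordinarily drift apart over such a period. One control per site gives no information on that.

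At stake is the main hypothesis. A figure presented as the likelihood of attribution would be read as causal evidence, although it would be close to a restatement of the within-series p-value.

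**Working it through.** **1. The plan's own figure.** 6 years × 4 = 24 quarters before and 3.5 × 4 = 14 after, total 38 per centre. This reproduces the stated 38.

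**2. What one control can estimate.** The between-centre variance of the pre-post change among untreated centres has (number of controls − 1) degrees of freedom. The smallest attainable rank p-value is 1/(controls + 1).

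| Untreated centres | df | 95% CI for drift SD, as multiples of the estimate | Smallest rank p |
|---|---|---|---|
| 1 (each pair) | 0 | not estimable | 0.50 |
| 2 (both pooled) | 1 | 0.45 to 31.9 | 0.33 |
| 10 | 9 | 0.69 to 1.83 | 0.09 |
| 20 | 19 | 0.76 to 1.46 | 1/21 = 0.048 |

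This step needs no assumption about the size of drift.

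**3. Whether the model's standard error registers drift.** Take one treated and one control centre, 24 + 14 quarters, independent residuals with SD 1, and an intercept, trend and level change for each centre.

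- Sum of squares of the post-period indicator: 24 × 14/38 = 8.842.
- Sum of squares of time: 38 × (38² − 1)/12 = 4569.5.
- Cross-product: 8.842 × 19 = 168, where 19 is the difference in mean time between the two periods.
- Left after removing trend: 8.842 − 168²/4569.5 = 2.665.
- Variance of the difference in level change: 2/2.665 = 0.750, so SE = 0.866.

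Now set the true HKTP effect to 0 and give each centre its own level shift at the interruption with SD τ, in residual-SD units (assumed; the documents give none). The actual variance of the estimate becomes 0.750 + 2τ², while the model still reports about 0.866. The two-sided 5% test then rejects when |t| exceeds 1.994 × 0.866/√(0.750 + 2τ²), with 70 df.

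- τ = 0.5: √1.250 = 1.118, giving a threshold of 1.545 and 12.7% rejection.
- τ = 1.0: √2.750 = 1.658, giving a threshold of 1.041 and 30.1% rejection.

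Simulation with 20,000 runs per value agrees. Here the probabilistic analysis is represented by draws of the fitted effect from its estimated sampling distribution.

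| τ | Mean model SE | Two-sided rejection | Draws put over 95% probability on a positive effect |
|---|---|---|---|
| 0 | 0.86 | 5.2% | 5.2% |
| 0.25 | 0.86 | 7.0% | 6.6% |
| 0.5 | 0.86 | 13.0% | 10.7% |
| 1.0 | 0.86 | 30.4% | 20.0% |
| 1.5 | 0.86 | 45.5% | 26.7% |

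The SE does not move with τ, so neither the test nor a probabilistic analysis built on it sees the drift.

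**4. Size on a count scale.** The model is a one-control binomial segmented model with true effect 0. Assumed counts are 3-6 Hispanic and 6-12 non-Hispanic white LDKTs per quarter, with centre drift on the log scale. Several sets of 800 to 4,000 runs per setting, with and without a slope-change term, give these one-sided false-positive rates against a nominal 2.5%:

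| Drift SD (log scale) | False benefit |
|---|---|
| 0 | about 2-4% |
| 0.1 | about 3% |
| 0.2 | about 4-6% |
| 0.3 | about 4-10% |
| 0.4 | about 7-14% |

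**The case against.** The other side has several good points.

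- **The one-way analysis is more than parameter-wiggling.** It looks for secular-trend thresholds, which is a tipping-point analysis. This stands, and it would be wrong to say the sensitivity work carries no information on rival causes. But a threshold has no probability attached.
- **The ratio already removes some rival causes.** Table 2 explains that centre-wide factors acting alike on both groups, with paired donation and desensitization as examples, are accounted for by the Hispanic to non-Hispanic white ratio. This stands. For that outcome the threat narrows to drift affecting the two groups differently. It does not protect the Hispanic LDKT count, which any centre-level drift can move.
- **Other safeguards exist.** The article plans contextual measures from all sites, news scans, intermediate outcomes at control sites, and regional adjustment using published and control-centre volumes. These help interpretation, but none is described as giving a distribution for centre-specific drift.
- **The source of the distributions is loosely worded.** The text does not say which data set the ranges. A bias analysis with an external drift distribution could give a conditional probability, but none is named.
- **The article makes no claim that one control estimates drift,** and it openly discusses why centres were not randomised. This stands: the single control is a design limit that leaves the attribution statement unsupported, not a contradiction in the text.

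A reader might also infer that the controls are unsuitable because the matching factors ("Intervention sites are matched with control sites by city population size, Hispanic proportion of the city population, and KT and LDKT volumes") omit the pre-period ratio and its trend. The documents do not support that as a fault. With 24 baseline quarters, segmented regression models each centre's own level and trend, so such matching would be desirable but is not required.

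**Conclusion.** The point holds in a limited form. The stated purpose does not follow from the stated method: the analysis gives, at best, the probability of a non-zero break if the segmented model is right and no other centre-specific change affecting Hispanic LDKTs coincided with the interruption. That conclusion and the 0 df per pair rest on the text and the design alone.

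The size of the error is conditional. A reader might infer that the nominal p-values are definitely too small. The documents do not establish this, since they give no drift SD and no quarterly counts. With drift SD of 0-0.1 the error rate is about nominal; at 0.3-0.4 it is roughly two to five times nominal (4% to 14% against 2.5%). The calculations also assume independent residuals, or independent counts, apart from the drift.

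This should be changed, because it governs how the main result will be read and the correction is cheap. It does not invalidate the interrupted time series or the matched-control comparison.

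**What to change.** 1. **Reword the purpose.** Describe the probabilistic analysis as parameter uncertainty conditional on the segmented model, and drop its attribution use. Present the one-way analysis as the amount of secular trend that would explain the result.
2. **Add a placebo-centre analysis for H1 and H2, as supporting evidence.** Run the same segmented model with the same break date on other OPTN/UNOS centres that meet volume and Hispanic-share limits fixed in advance. Report each intervention centre's rank among them. At least 19 placebo centres are needed for a rank p-value of 0.05 and 39 for 0.025 (1/20 and 1/40). The documents do not say how many centres would qualify, so the attainable p-value should be stated once the limits are set. The rank shows how unusual the change is among comparable centres; it is still not a probability of attribution.
3. **Keep the named matched controls as planned,** including for medical-record outcomes. A synthetic control weighted on the pre-period series is optional.

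The cost is some analyst time, since the H1 and H2 data are public and centre-level and no new sites or patients are needed. The downside is that the rank-based p-value may be less favourable than the within-series one.
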